## Abstract

**Background:**

*Symptomatic and asymptomatic enteric infections* in early childhood are associated with negative effects on childhood growth and development, especially in low and middle-income countries, and food may be an important transmission route. Although basic food hygiene practices might reduce exposure to faecal pathogens and resulting infections, there have been few rigorous interventions studies to assess this, and no studies in low income urban settings where risks are plausibly very high. The aim of this study is to evaluate the impact of a novel infant food hygiene intervention on infant enteric infections and diarrhoea in peri-urban settlements of Kisumu, Kenya.

**Methods:**

This is a cluster randomized control trial with 50 clusters, representing the catchment areas of Community Health Volunteers (CHVs), randomly assigned to intervention or control, and a total of 750 infants recruited on a rolling basis at 22 weeks of age and then followed for 15 weeks. The intervention targeted four key caregiver behaviours related to food hygiene: 1) hand washing with soap before infant food preparation and feeding; 2) bringing all infant food to the boil before feeding, including when reheating or reserving; 3) storing all infant food in sealed containers; and, 4) using only specific utensils for infant feeding which are kept separate and clean.

**Results:**

The primary outcome of interest is the prevalence of one or more of 23 pre-specified enteric infections, determined using quantitative real-time polymerase chain reaction for enteric pathogen gene targets. In addition, infant food samples were collected at 33 weeks, and faecal indicator bacteria (*Enterococcus*) isolated and enumerated to assess the impact of the intervention on infant food contamination.

**Conclusion:**

To our knowledge this is the first randomized controlled trial to assess the effect of an infant food hygiene intervention on enteric infections in a high burden, low income urban setting. Our trial responds to growing evidence that food may be a key pathway for early childhood enteric infection and disease and that basic food hygiene behaviours may be able to mitigate these risks. The Safe Start trial seeks to provide new evidence as to whether a locally appropriate infant food hygiene intervention delivered through the local health extension system can improve the health of young children.

**Trial registration:**

The trial was registered at clinicaltrial.gov on March 16th 2018 before enrolment of any participants (https://clinicaltrials.gov/ct2/show/NCT03468114).

## Background

Diarrhoeal disease, a key symptom of gastro-intestinal or enteric infection, is the fourth leading cause of disability globally [1] and the leading cause of child death in sub-Saharan Africa [2]. Furthermore, there is growing evidence of the impact of sub-clinical childhood enteric infection and disease on growth and development [3, 4].

Food is likely to be an important source of exposure to enteric pathogens in early childhood. Recent studies have shown that food given to children in early childhood can be highly contaminated with faecal indicator bacteria [5] as well as specific diarrhoeagenic enteric pathogens [6]. Environmental interventions to reduce exposure to these pathogens and reduce diarrhoea have traditionally focused on improving the quality and distribution of drinking water, the management of excreta through sanitation systems and the promotion of handwashing with soap at critical times [7] but generally not on food hygiene related behaviours and infrastructure.

More than half of the world’s population now reside in urban areas and over one third of this population live in ‘slums or informal settlements’ [8]. Although access to safe water and sanitation is generally higher in urban areas [9], the risk of enteric infection may be greatest in poor urban areas due to the combination of high population density and limited public health infrastructure [10–13]. These conditions pose multiple risks for contamination of food as supported by a recent study of pathogen diversity in infant food in low-income informal neighbourhoods of Kisumu, Kenya [6]. The ‘Safe Start’ trial is designed to assess whether a locally appropriate, low-cost food hygiene intervention, delivered within the context of the existing health extension system in peri-urban neighbourhoods of Kisumu, Kenya can reduce early childhood exposure to enteric pathogens.

## Methods

### Research aim and objectives

The purpose of this study is to examine the effect of an infant food hygiene behaviour change intervention on child health. The study will assess the impact of the intervention on: (1) infant health as determined by prevalence of gastro-intestinal infection and diarrhoeal; (2) specific food hygiene practices; and (3) infant food contamination.

### Study design

Our study was a cluster randomized controlled trial (cRCT) design. Clusters for the trial were defined as the catchment areas of local Community Health Volunteers (CHVs); a total of 50 CHV catchment areas were recruited into the study and randomly assigned to an intervention and control arm of the study. An overview of the study design is presented in Fig. 1 (CONSORT [14] diagram).

**Fig. 1 Fig1:**
[figure not shown]
– CONSORT diagram

The primary outcome for the study is the prevalence of enteric infection at age 37 weeks (+/− 1 week). We define the prevalence of enteric infection as the presence of 1 or more enteric pathogens in child stools based on the detection of 23 genetic markers of specific common enteric bacteria, viruses and protozoan (Table 1). The secondary outcome is diarrhoea; defined as the number of days a child has diarrhoea between 22 and 37 weeks of age (+/− 1 week). Tertiary outcomes include child mortality, defined as any infant death occurring between 22 and 37 weeks of age (+/− 1 week). In addition, the study will assess the effectiveness of the intervention by measuring changes in specific food practices and in bacterial contamination of infant food.

**Table 1 Tab1:** – Specific enteric pathogen primers and probes for TaqMan Array Card used to determine the primary outcome

PATHOGEN	GENE TARGET	FORWARD PRIMER	REVERSE PRIMER	PROBE SEQUENCE	Ref
BACTERIA					
Aeromonas	Aerolysin	TYCGYTACCAGTGGGACAAG	CCRGCAAACTGGCTCTCG	CAGTTCCAGTCCCACCACTT	[2]
*Campylobacter jejuni/C. coli*	*cadF*	CTGCTAAACCATAGAAATAAAATTTCTCAC	CTTTGAAGGTAATTTAGATATGGATAATCG	CATTTTGACGATTTTTGGCTTGA	[2]
*Clostridium difficile*	*tcdB*	GGTATTACCTAATGCTCCAAATAG	TTTGTGCCATCATTTTCTAAGC	CCTGGTGTCCATCCTGTTTC	[2]
Enteroaggregative *Escherichia coli* (EAEC)	*aaiC*	ATTGTCCTCAGGCATTTCAC	ACGACACCCCTGATAAACAA	TAGTGCATACTCATCATTTAAG	[2]
Enteroaggregative *Escherichia coli* (EAEC)	*aatA*	CTGGCGAAAGACTGTATCAT	TTTTGCTTCATAAGCCGATAGA	TGGTTCTCATCTATTACAGACAGC	[2]
Enterohemorrhagic *E. coli* (EHEC) 0157	*rdbE*	TTTCACACTTATTGGATGGTCTCAA	CGATGAGTTTATCTGCAAGGTGAT	CTCTCTTTCCTCTGCGGTCCT	[1]
Enteropathogenic *E. coli (*EPEC)	*eae*	CATTGATCAGGATTTTTCTGGTGATA	CTCATGCGGAAATAGCCGTTA	ATACTGGCGAGACTATTTCAA	[2]
Enteropathogenic *E. coli (*EPEC)	*bfpA*	TGGTGCTTGCGCTTGCT	CGTTGCGCTCATTACTTCTG	CAGTCTGCGTCTGATTCCAA	[2]
Enterotoxigenic *E. coli* (ETEC) LT toxin	ETEC LT	TTCCCACCGGATCACCAA	CAACCTTGTGGTGCATGATGA	CTTGGAGAGAAGAACCCT	[2]
Enterotoxigenic *E. coli* (ETEC) ST toxin	STh STp	GCTAAACCAGYAGRGTCTTCAAAATGAATCACTTGACTCTTCAAAA	CCCGGTACARGCAGGATTACAACATGAATCACTTGACTCTTCAAAA	TGGTCCTGAAAGCATGAATGAACAACACATTTTACTGCT	[2]
*Salmonella enteritidis*	*ttr*	CTCACCAGGAGATTACAACATGG	AGCTCAGACCAAAAGTGACCATC	CACCGACGGCGAGACCGACTTT	[2]
*Shigella* spp.	*virG*	TCAGAAAGGTAATTGGCATGGA	AGAACCGCGCCCAAAGA	AGGGCGGAATATT	[1]
*Vibrio cholerae*	*hlyA*	ATCGTCAGTTTGGAGCCAGT	TCGATGCGTTAAACACGAAG	ACCGATGCGATTGCCCAA	[2]
PROCESS CONTROL					
MS2	MS2g1	TGGCACTACCCCTCTCCGTATTCAC	GTACGGGCGACCCCACGATGAC	CACATCGATAGATCAAGGTGCCTACAAGC	[2]
VIRUS					
Adenovirus 40–41	Fiber Gene	AACTTTCTCTCTTAATAGACGCC	AGGGGGCTAGAAAACAAAA	CTGACACGGGCACTCT	[2]
Adenovirus broad species	Hexon	GCCACGGTGGGGTTTCTAAACTT	GCCCCAGTGGTCTTACATGCACATC	TGCACCAGACCCGGGCTCAG	[1]
Norovirus GI	ORF 1–2	CGYTGGATGCGNTTYCATGA	CTTAGACGCCATCATCATTYAC	TGGACAGGAGATCGC	[1]
Norovirus GII	ORF 1–2	CARGARBCNATGTTYAGR TGGATGAG	TCGACGCCATCTTCATTCACA	TGGGAGGGCGATCGCAATCT	[2]
Rotavirus	NSP3	ACCATCTWCACRTRACCCTCTATGAG	GGTCACATAACGCCCCTATAGC	AGTTAAAAGCTAACACTGTCAAA	[2]
PROTOZOAN					
*Giardia duodenalis* Assemblage A	*triosephosphate isomerase (TPI)*	TTCCGCCGTACACCTGTC	GCGCTGCTATCCTCAACTG	ATTGCGGCAAACACGTCA	[1]
*Giardia duodenalis* Assemblage B	*triosephosphate isomerase (TPI)*	GATGAACGCAAGGCCAATAA	CTTTGATTCTCCAATCTCCTTCTT	AATATTGCTCAGCTCGAGGC	[1]
*Cryptosporidium spp*.	18 s rRNA	GGGTTGTATTTATTAGATAAAGAACCA	AGGCCAATACCCTACCGTCT	TGACATATCATTCAAGTTTCTGAC	[2]
*C. hominus*	LIB13	TCCTTGAAATGAATATTTGTGACTCG	AAATGTGGTAGTTGCGGTTGAAA	CTTACTTCGTGGCGGCGT	[1]
*C. parvum*	LIB13	TCCTTGAAATGAATATTTGTGACTCG	TTAATGTGGTAGTTGCGGTTGAAC	TATCTCTTCGTAGCGGCGTA	[1]

### Study setting

The study is being conducted in two informal neighbourhoods of Kisumu, Kenya: Nyalenda A and Nyalenda B (Fig. 2). Kisumu is the third largest city in Kenya and is located in Kisumu County, on the shores of Lake Victoria, and has a population of approximately 400,000. The city is surrounded by a series of peri-urban areas sometimes referred to as the ‘slum belt’ [15]. These peri-urban areas have emerged due to economic migration and a lack of affordable housing [16]. Some sources estimate that up to 60% of the city’s population reside in these peri-urban communities [17].

**Fig. 2 Fig2:**
[figure not shown]
– Map showing Safe Start study areas of Nyalenda A and B (pink), two of the informal neighbourhoods around Kisumu Town in Kisumu County, Kenya

The counties that previously made up the Nyanza and Western provinces have relatively high levels of infectious disease morbidity and mortality. The child mortality rate for Kisumu county is 105 deaths per 1000 live births and the prevalence of childhood stunting (below-2 SD) is approximately 25% [18]. In Kisumu county, approximately 70% of all children between 12 and 23 months of age have received all recommended child disease vaccines, and it is estimated that 30% of children experiencing diarrhoea receive timely oral rehydration therapy [ORT] [18]. Two-week diarrhoeal prevalence in Kisumu is 18%, higher than neighbouring areas [18]. Data from the nearby Kenyan site of the Global Enteric Multi-site Study (GEMS) [19] reported the leading identified infectious causes of diarhhoea to be Rotavirus, *Cryptosporidium*, ST-ETEC and *Shigella*.

### Community health volunteer system

Kenya has been undergoing a process of decentralization, with many areas of policy, including the health sector and the community extension services, now the responsibility of the County Government. The Community Health Committee (CHC), is the health governance structure closest to the people at the county level. Community Health Volunteers (CHVs), who serve as frontline health workers in this decentralized system, report to the community health committee through the Community Health Extension Workers (CHEW) [20].

CHVs receive basic training to diagnose and treat illnesses such as malaria, pneumonia, and diarrhoea; make referrals to health facilities; provide health education; conduct nutrition surveillance; collect vital events data; assist with immunization and provide other aspects of maternal and child health [21, 22]. More recently, CHVs have been engaged in the promotion of some hygiene-related behaviour, including community led total sanitation (CLTS) and safe household water storage and treatment [23]. Under the current study, we collaborated with CHVs to design and test an intervention to reduce infant exposure to enteric pathogens and they are involved in the delivery of the intervention.

### Study participants

Our primary participants are infants enrolled at the age of 22 weeks (+/− 1 week), who currently reside in Nyalenda A or B, and will be living there for the subsequent five months. Our secondary participants are primary or secondary caregivers who provide care to the infant during the day and who are at least 18 years of age. A primary caregiver is defined as the person who is directly responsible for the enrolled child and a secondary caregiver is defined as any other person apart from the primary caregiver who watches the child or supports the primary caregiver.

### The Safe Start intervention

#### Development of intervention

We followed the Behaviour Centered Design (BCD) approach to intervention development [24]. Specific qualitative and quantitative formative research studies were implemented in a similar and neighbouring area of Kisumu city. Infant faecal-oral exposure in their domestic environment was assessed using structured observation of infants and caregivers, identifying low rates of hand hygiene among caretakers and infant food as a viable route of exposure to enteric pathogens that could be mitigated by safe preparation, storage and reheating of food [25]. Caregiver attitudes and practices in this population and the emotional and environmental drivers of food hygiene behaviours were assessed through structured observation and in-depth interviews with primary and secondary caregivers [26]. Microbiological and molecular analysis of infant food samples was used to determine the prevalence and intensity of infant food contamination with specific enteric pathogens implicated in childhood diarrhoea [6]. Various known diarrhoeagenic agents, including bacteria, viruses and protozoa, were frequently detected with at least one enteric pathogen identified in 62% of infant food samples and multiple pathogens identified in 37% of infant food. A fourth study that specifically informed Safe Start intervention delivery explored CHV schedules, routines and capacity to deliver behaviour change through direct observation, interviews, and focus group discussions. This study identified a wide range of challenges, including: poor training, lack of material resources, and limited incentives to undertake additional tasks [23].

Formative research findings led to the design of two primary candidate intervention components designed to improve food hygiene behaviours in the target population. The first component consisted of hardware items introduced at the household level to facilitate improved food hygiene behaviours. The second component consisted of motivational and educational messaging designed to improve caregiver knowledge of proper food hygiene and target the specific emotional drivers of safe food hygiene identified in formative research. The feasibility and acceptability of the two intervention components – both independently and in combination– were assessed and iteratively adapted using the Trials of Improved Practice (TIPs) methodology [27]. Details of this process are described in Simiyu et al. [28].

#### Intervention description

The final intervention was designed to target early childhood exposure to enteric pathogens through contaminated food. The intervention targets the following four behaviours:
Safe hand hygiene: handwashing with soap before food preparation and before infant feeding.Safe food preparation: bringing all infant food to the boil before any feeding event.Safe storage of food: storing all infant food in sealed containers.Safe feeding: using designated utensils for infant feeding reserved from other use.

The intervention components use two sequential and complementary aspects of the nurture motives. The first is the desire to care for and protect a child as they grow. In formative research, “happy” was seen as marker of child fitness and health. The concept of “Happy Baby” emerged as a focal point for messaging and was incorporated into intervention materials. The second commonly articulated aspect of nurture was the desire to ensure that the child will have a successful future. This was operationalized as messages related to a “Successful Child” and focused on ensuring that the mother provides the necessary foundation for future success. In addition to messages targeting emotional drivers, the intervention also provides the necessary foundational knowledge about food hygiene, and associated risks, but framed within an emic understanding of child health and successful parenting within the communities.

The intervention is delivered in four visits (Fig. 3) in collaboration between CHVs and specifically trained field staff. Visit 1 is a preliminary sensitization visit, led by participating CHVs in the weeks before children turn six months of age. During this first visit, CHVs reiterate existing messages regarding the importance of exclusive breastfeeding until 6 months of age, appropriate weaning foods, and their introduction after six months. The CHV also introduces new topics regarding food hygiene, including: environmental contamination, the risks associated with contaminated weaning food, and the potential health consequences - diarrhoeal disease, growth impairment, and cognitive deficits. The second visit is timed to coincide with children turning 6 months (25 weeks) old and introduces the “Happy Baby” aspect of the intervention. This household visit is designed to be a fun and lively experience for participating households and is led by specifically trained field staff who are accompanied by local CHVs. During this visit, field staff deliver a number of products designed to enable and trigger improved food hygiene practices, including: a baby bowl, a baby spoon, a baby cup, a handwashing container/station, a bottle dispenser of liquid soap (with instructions for self-refill), two deep and two rectangular sealable storage containers, and a branded “Happy Baby” feeding mat. In addition, intervention households receive a “Happy Baby” customised calendar with images that reinforce target behaviours and reference newly provided materials. Caregivers are instructed to record diarrhoea episodes on calendars between visits, ensuring that caretakers interact with and see messages. Visit 3 occurs when the child is 29 weeks old. This visit, once again lead by local CHVs, reinforces messages, discusses experiences with new target behaviours, and reviews new information on food hygiene. Visit 4 occurs when the child is 32 weeks old and introduces the “Successful Child” component of the intervention. Successful child images compliment “Happy Baby” materials by including images of older children in graduation gowns and caps. The successful child stage includes a “graduation event” for the caregiver, including a “food hygiene pledge”, and a forward-looking discussion about their aspirations for the infant and how to give their child a “Safe Start” in life. As an example of the materials, we include an image of the “Successful Girl” calendar given to caregivers in the intervention group (Additional file 1).

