#### Sample size calculation and analysis

Using a standard approach for calculating sample size for cluster Randomised Controlled Trials [30] we estimated the minimum detectable difference in primary and secondary health outcome measures with a planned total sample size of 750 children (375 intervention, 375 controls) across 50 clusters (25control/25 intervention) and with an anticipated intra-class correlation co-efficient (ICC) of 0.01. Our assumptions regarding baseline/control prevalence of any enteric infection and diarrhoeal disease are drawn from the most recent Multiple Indicator Cluster Survey (MICS) estimates for the prevalence of stunting and recent diarrhoea in Nyanza province [18], and the Demographic and Health Surveillance (DHS) survey national urban estimates for Kenya [31]; alongside, the national (Kenyan) and global estimates for prevalence of any enteric infection from the Global Enteric Multi-country Study (GEMS) [19]. In the absence of published effect size estimates for similar early childhood interventions on enteric infection prevalence and our assumption regarding effect size is cautiously estimated based on the effects on diarrhoea of different WASH interventions [32].

For the primary outcome, with 750 infants enrolled, and assuming a control prevalence of ≥1 of the 23 measured enteric infections of 0.7, and an intraclass correlation coefficient (ICC) of 0.01 we would have 80% power at a 5% level of significance to detect a minimum difference between arms in the prevalence of ≥1 infection of 11%. For our secondary outcome, with 750 infants, we would be able to detect a minimum difference in longitudinal prevalence of caregiver reported diarrhoea of 7% or greater, assuming a control longitudinal prevalence of diarrhoea of 15%.

The CONSORT Statement for cluster randomised controlled trials will guide the analysis and presentation of results [33]. To assess any imbalance between arms, descriptive statistics of demographic and outcome measures (where available) will be tabulated at baseline.

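### Recording diarrhoea on a calendar is described only as part of the intervention, so noticing and recall of the caregiver-reported secondary outcome are likely to differ by arm

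*Protocol article*

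**What the plan says.** Under Intervention description, the protocol article lists a customised calendar among the items that intervention households receive at the second visit, when the child is 25 weeks old. The next sentence is: "Caregivers are instructed to record diarrhoea episodes on calendars between visits, ensuring that caretakers interact with and see messages". The reason given is exposure to the messages, which makes the recording task part of the intervention. The same section ends with a second, later calendar, described as a "calendar given to caregivers in the intervention group (Additional file 1").

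Under Data collection, the article lists questionnaires at 22, 33 and 37 weeks, a structured observation, and stool and food samples. It lists no diary or calendar for either arm.

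The secondary outcome, in the text below Fig. 1, is diarrhoea, "defined as the number of days a child has diarrhoea between 22 and 37 weeks of age". Sample size calculation and analysis calls it "longitudinal prevalence of caregiver reported diarrhoea" and gives it a power statement of its own. The Blinding section says that participants could not be blinded.

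**The concern.** The intervention asks caregivers to notice, write down and so remember the events that the secondary outcome counts. If control caregivers have no such task, they answer the same questions from unaided memory, and the first follow-up questionnaire comes 11 weeks after baseline (22 to 33 weeks). The arms would then differ in how completely diarrhoea is reported as well as in how much of it occurs.

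This difference arises after randomisation. The planned analysis by arm as randomised, GEE for clustering and adjustment for the baseline cluster mean do not remove it. Blinding the enumerators and the statistician does not equalise what caregivers remember. At stake is whether the diarrhoea comparison can be interpreted, in either direction.

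**Working it through.** **Inputs from the protocol article (Sample size calculation and analysis)**
- Size: "750 children (375 intervention, 375 controls) across 50 clusters (25control/25 intervention"), which is 375/25 = 15 infants per cluster.
- Clustering: "anticipated intra-class correlation co-efficient (ICC) of 0.01".
- Secondary outcome: "minimum difference in longitudinal prevalence of caregiver reported diarrhoea of 7% or greater", "assuming a control longitudinal prevalence of diarrhoea of 15"%.
- 80% power and 5% significance, taken as two-sided.

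**Inputs from other sections**
- Calendars start at 25 weeks (Intervention description).
- The outcome window is 22 to 37 weeks, or 15 weeks (text below Fig. 1).

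**Step 1: reproduce the plan's figure**
- Design effect = 1 + (15 − 1) × 0.01 = 1.14. Effective n per arm = 375/1.14 = 328.9.
- For 15% v 8%, the mean proportion is 0.115. The null standard error is √(2 × 0.115 × 0.885/328.9) = 0.0249, and the alternative standard error is √((0.1275 + 0.0736)/328.9) = 0.0247.
- Power = Φ((0.07 − 1.96 × 0.0249)/0.0247) = 0.805.

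The 7-point figure reproduces. It assumes that diarrhoea is reported equally well in both arms.

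**Step 2: assumptions for the illustration (not in the documents)**
- Unaided recall captures a share c of the days that a fully kept calendar captures, with c between 0.6 and 0.9.
- Every intervention caregiver keeps the calendar fully from week 25.
- Diarrhoea is spread evenly over the window, so 3 of 15 weeks (20%) are unaided in both arms.
- Longitudinal prevalence is treated as a proportion, as in step 1.

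Control observed = 0.15 × c. Intervention observed = true prevalence × (0.2c + 0.8).

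**Step 3: no true effect (15% in both arms)**

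Spurious excess = 0.15 × (0.2c + 0.8) − 0.15c = 0.12 × (1 − c).
- c = 0.9: 1.2 points.
- c = 0.8: 2.4 points (12.0% v 14.4%). The chance of a significant false harm is about 15%, against 2.5% with equal reporting.
- c = 0.6: 4.8 points.

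**Step 4: true effect as planned (15% v 8%), c = 0.8**
- Control 0.15 × 0.8 = 0.120. Intervention 0.08 × 0.96 = 0.0768. Observed difference 4.3 points.
- Null standard error √(2 × 0.0984 × 0.9016/328.9) = 0.0232. Alternative standard error √((0.1056 + 0.0709)/328.9) = 0.0232.
- Power = Φ((0.0432 − 1.96 × 0.0232)/0.0232) ≈ 0.46.

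For comparison, equal 80% capture in both arms gives 12% v 6.4% and power of about 70%. Of the fall from about 80% to 46%, roughly 10 points are therefore due to under-reporting as such, and about 24 to the difference between arms.

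**Step 5: the opposite direction**

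If unblinded intervention caregivers under-report (70% reported, against 90% in control) and there is no true effect, the observed prevalences are 0.15 × 0.9 = 13.5% and 0.15 × 0.7 = 10.5%. The chance of a significant false benefit is then about 22%.

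**The case against.** Several points on the other side stand.

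**The absence of a control calendar is inferred.** A reader might conclude that controls certainly receive none. No sentence says so, the instruction to record does not itself name an arm, and the schedule figure is not available here. The inference rests on placement, on two phrases tying calendars to the intervention group, and on the stated purpose of message exposure. It is the natural reading, but not a stated fact.

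**The calendar is not named as an outcome instrument.** A reader might infer that the measuring tool itself differs by arm. The documents do not support that: Data collection lists questionnaires, and calendars are not among the data sources. What remains is an effect on noticing and recall. Its size depends on the questionnaire's recall period, which the article does not give and may leave to the full protocol. A short recall period would make it smaller.

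**The direction is not fixed.** A reader might infer that the bias can only hide benefit. Intervention caregivers are unblinded and make a food hygiene pledge at visit 4, so they may under-report.

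**The illustration is an upper case for its capture rates.** It assumes full calendar use. If the calendar covered half of the days after week 25, the null excess would halve to 0.06 × (1 − c), or 0.6-2.4 points.

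None of this removes the core point. As described, one unblinded arm is prompted on a named, powered outcome and the other is not.

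**Conclusion.** The concern holds in a limited form. Noticing and recall of diarrhoea are likely to differ between arms, whether or not calendar entries are used as data, and the planned analysis cannot correct for it. On the assumptions in step 2, the distortion is about 1.2-4.8 points under no effect, set against a planned detectable difference of 7 points. At 80% capture, power falls to about 46%. The capture rates are assumptions, not figures from the documents, and the sign of the bias cannot be settled from them. Only the secondary diarrhoea outcome is affected, because the primary outcome is PCR on stool and does not rest on caregiver report. The planned sample size need not change. Should-fix, moderate confidence.

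**What to change.** 1. State that the diarrhoea outcome is derived only from the same questionnaire item, with the same recall period, in both arms, and never from calendar entries. Say what control households receive.
2. Make the prompting equal. Either give control households a plain, unbranded record form with the same instruction, or replace the diarrhoea-recording task on the intervention calendar with one that does not record an outcome.
3. Trial status gives March 26th, 2018 as the start of recruitment, so apply any change to both arms from one date. Analyse infants before and after that date separately as a sensitivity analysis.
4. For infants already followed, report differential ascertainment as a limitation. The article's Limitations section does not mention it.

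The cost is a printed sheet or one changed instruction, a sentence of outcome wording and one sensitivity analysis. The downsides are small: some self-monitoring among controls if they get a form, or a slightly altered message-exposure device if the task is replaced.
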